### Quality control

This trial adheres to Good Clinical Practice (GCP) standards and meets the requirements set by the Ethics Committees. It is conducted under the supervision of the Ethics Committees at the participating institutions. A Data Safety Monitoring Board (DSMB) will be established, comprising two independent neonatologists and an independent statistician. The DSMB will have designated review points to assess trial progress and safety.

In clinical practice, neonatologists receive training on MISA and DCC before rotating to the NICU, and undergo regular assessments. This ensures that there are neonatologists proficient in MISA and DCC on duty 24 h a day, who can perform the corresponding clinical procedures for preterm infants delivered at any time. Upon entering the NICU, nasal continuous positive airway pressure (NCPAP) or nasal intermittent positive pressure ventilation (NIPPV) will be initiated as the first line of non-invasive respiratory support. During MISA, the infant is placed in an incubator with the temperature set at 37°C. The infant's limbs are properly swaddled to soothe them, preventing crying and injury. A laryngoscope is used to expose the glottis, and a thin catheter is inserted under the maintenance of non-invasive ventilation support, with the insertion depth calculated as (infant's weight in kg) + 5.5/6 cm. Pulmonary surfactant (Curosurf, 200 mg/kg or Calf Pulmonary Surfactant for Injection, 100 mg/kg) is slowly instilled, with the total administration time being approximately 3 min. If the infant cries or experiences a drop in heart rate or oxygen saturation, the administration is paused; it is resumed after the infant's condition stabilizes until the full dose is administered.

In collaboration with the obstetrics department, operational protocols for DCC during deliveries in the labor room and operating room have been developed. Monthly training on neonatal resuscitation for asphyxia and DCC is provided to midwives and obstetricians, ensuring that the condition of newborns is quickly evaluated during delivery and that safe DCC is performed for those without contraindications.

### Outcome measures

#### Primary outcome measure

The primary outcome is the survival rate and incidence of BPD at a corrected gestational age of 36 weeks.

Diagnosis and classification of bronchopulmonary dysplasia will follow the International Workshop BPD classification standards proposed by the US NICHD in 2019 (12).

#### Secondary outcome measures

The secondary outcomes are as follows:
Rate of hsPDARate of air leakage, pulmonary hemorrhage, and infectious pneumoniaRate of late-onset sepsis with positive blood cultureRate of retinopathy of prematurity (ROP)Rate of grade III-IV periventricular intraventricular hemorrhage (IVH) and periventricular leukomalacia (PVL)Rate of neonatal necrotizing enterocolitis (IIA or above)Duration of NCPAP/NIPPV, duration of IMV, and days on supplemental oxygenLength of hospitalization and associated costs for care and treatmentMortality rates during the first week after birth and throughout hospitalizationHemoglobin and hematocrit levels within 24 h after birth, and timing of blood transfusions during hospitalizationIncidence and duration of hyperbilirubinemia

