## Background

With the rapid advancement of neonatal intensive care technology, the survival rate of premature infants born at less than 30 weeks gestation continues to rise. However, the immaturity of various organ systems leads to a high incidence of complications, and long-term outcomes can often be less than optimistic (1). Consequently, enhancing both short-term and long-term prognoses for these infants through quality improvement initiatives has become a prominent focus in recent clinical research.

BPD is a critical complication in very premature infants, significantly affecting their future survival, as well as their respiratory and neurological development. Preventing and reducing the incidence of BPD is crucial for improving the overall prognosis of these infants (2). Ensuring postpartum respiratory and circulatory stability while minimizing exposure to early invasive mechanical ventilation is essential for preventing and reducing the incidence of BPD.

The management of respiratory and circulatory conditions in preterm infants begins with DCC in the delivery room. Compared to ICC, DCC facilitates the transfer of blood from the placenta to the infant, enhancing the adaptability of vital organs such as the heart, brain, and lungs. This practice supports a smoother transition from intrauterine to extrauterine life, promotes the conversion of respiratory circulation, and can reduce preterm infant mortality by 30%. Additionally, DCC decreases the incidence of complications such as intraventricular hemorrhage, necrotizing enterocolitis, and late-onset sepsis. It also increases blood volume, minimizes the need for blood transfusions, enhances iron storage, and lowers the risk of long-term neurodevelopmental issues. Therefore, DCC emerges as a viable strategy to enhance the perinatal prognosis of preterm infants (3–7).

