#### Exclusion criteria

① Premature infants who have received tracheal intubation prior to the use of PS due to resuscitation or other reasons shortly after birth;② Premature infants with identified or confirmed congenital abnormalities (such as fetal edema, chylothorax, or neuromuscular disease) or severe birth complications (including hemorrhagic shock, air leakage, or early-onset sepsis) that impact respiratory function;③ Newborns who discontinue treatment or have incomplete information;④ Newborns involved in other intervention research studies.

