### Sample size calculation

Our hospital has previously conducted a prospective multicenter clinical study comparing MISA and tracheal intubation in the early stages. The results indicated that the incidence of BPD in premature infants with a gestational age of less than 30 weeks was 29% in the MISA group (*n* = 31) and 70% in the tracheal intubation group (*n* = 20). Assuming the BPD incidence rate (p_1_) in the ICC + MISA group for this study is 29%, and the incidence in the DCC + MISA group (p_2_) decreases by 15%–14%, we will set the Type I error (α) at 0.05 and the Type II error (β) at 0.2. With a sample size ratio (k) of 3:1 between the DCC + MISA and ICC + MISA groups, the sample size calculation formula is:$$n_{2}=\frac{{\left(z_{1-a/2}+z_{1-\beta }\right)}^{2}[\;p_{1}(1-p_{1})/k+p_{2}(1-p_{2})]}{{\left(\;p_{1}-p_{2}\right)}^{2}}$$*n*_1_ = *k* × *n*_2_.

Where z_(1−*α*/2)_ = 1.96 and _z(1−*β*)_ = 0.84.

This results in a sample size of 66 for the DCC + MISA group and 198 for the ICC + MISA group. Assuming a 10% loss to follow-up, the adjusted sample sizes will be 74 for the DCC + MISA group and 222 for the ICC + MISA group. Additionally, the sample size for the ICC + tracheal intubation group is also set at 222 cases.

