### Statistical analysis

Statistical analyses were conducted using SPSS 20.0 software. Normally distributed data are presented as mean ± standard deviation, with intergroup comparisons performed using one-way analysis of variance (ANOVA) and *post hoc* tests conducted via the Student-Newman-Keuls (SNK) method for Type I error correction. Non-normally distributed data are expressed as median (Q1, Q3), and intergroup comparisons are made using the Kruskal–Wallis test.

For categorical data, counts and percentages are used for intergroup comparisons, employing the *χ*² test with continuity correction or Fisher's exact test as appropriate. The analysis of factors influencing binary outcomes will be performed using binary logistic regression, accounting for potential confounding variables. A *p*-value of <0.05 will be considered statistically significant.

To assess the robustness of the main conclusions of the study, we will conduct the following sensitivity analyses: To control for potential confounding factors as comprehensively as possible, we will include all baseline variables with intergroup differences reaching a significance level of *P* < 0.1 in the univariate analysis, together with the study grouping variable, into the multivariable Logistic regression model. This is to calculate the adjusted odds ratio (aOR) of the effect of DCC + MISA on BPD and its 95% confidence interval (95% CI).

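### Respiratory-support, oxygen and hospital-stay durations have no rule for death, so differences in survival between the three groups can distort the comparison

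*Protocol article*

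**What the plan says.** Under Secondary outcome measures, the article lists duration of NCPAP/NIPPV, "duration of IMV, and days on supplemental" oxygen, and then length of stay with its costs. Each is a plain duration or total. Deaths in the first week and before discharge appear in the same list as separate outcomes.

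Under Statistical analysis, normally distributed data go to one-way ANOVA with SNK post hoc tests. For the rest: "Non-normally distributed data are expressed as median (Q1, Q3), and intergroup comparisons are made using the Kruskal–Wallis test". Regression adjustment is described for binary outcomes only.

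The article gives no rule for how a death enters a duration. Death is not an exclusion. The nearest criterion is "Newborns who discontinue treatment or have incomplete information", which may remove some deaths but is not worded to remove all of them.

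Survival is an explicit target: "The primary outcome is the survival rate and incidence of BPD at a corrected gestational age of 36 weeks". The Background says of DCC that it "can reduce preterm infant mortality by 30" per cent, and that survival below 30 weeks is still rising.

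**The concern.** Support, oxygen and stay all end at death. An infant who dies on day 7 has at most about a week of each, and a rank test or a mean treats that as a favourable result. If one group keeps more infants alive, its stay, oxygen and non-invasive support times lengthen without any respiratory harm. Conversely, a regimen with more early deaths can look more efficient.

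The groups come from three successive periods (2017–2020, 2021–2024, and August 2025 to October 2027), so survival could differ through general progress in care even if cord management had no effect. The article intends the comparison of efficacy and safety to inform treatment decisions, so a reader must be able to tell whether a longer duration means more illness or fewer deaths.

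**Working it through.** **What the plan's figures provide.** The article gives no expected value for any duration and no mortality rate. Its only calculation is for BPD, and it supplies the group sizes used below. With p1 = 0.29, p2 = 0.14 and k = 3:

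n2 = (1.96 + 0.84)² × [0.29 × 0.71/3 + 0.14 × 0.86] / 0.15² = 7.84 × 0.18903 / 0.0225 = 65.87, so 66.

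Then 3 × 66 = 198; 66/0.9 = 73.3, so 74; and 3 × 74 = 222. The stated sizes reproduce and are not affected by this point.

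**Effect on a mean.** Let m be mortality, s the mean duration in survivors and d the mean duration in infants who die. The group mean is (1 − m)s + md. If mortality falls to 0.7m and s and d do not change, the mean shifts by 0.3m(s − d). Assume, for illustration only, s = 35 and d = 7 days of support:

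- m = 10%: 0.90 × 35 + 0.10 × 7 = 32.2, against 0.93 × 35 + 0.07 × 7 = 33.0; shift 0.8 days.
- m = 15%: 30.8 against 32.1; shift 1.3 days.
- m = 20%: 29.4 against 31.1; shift 1.7 days.

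The sign depends on s − d. For stay, oxygen and non-invasive support, s > d is to be expected when deaths are early. For IMV it is not established. Infants intubated before surfactant are excluded and first-line support is non-invasive, so some survivors may have no IMV days, while an infant who dies may have been ventilated. A death after 3 days of IMV ranks better than a survivor with 10 days, but worse than a survivor with none.

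**Effect on the rank test.** Length of stay was simulated for DCC+MISA (74) against ICC+MISA (222), 3,000 runs per row, with the Mann–Whitney test (the two-group form of Kruskal–Wallis). Assumptions, none from the article: the same log-normal stay in both groups (median 60 days, log-SD 0.35); exponential time to death with median 7 days in infants who die; deaths kept at their shortened stay; deaths unrelated to the stay an infant would otherwise have had. Differences are DCC+MISA minus ICC+MISA.

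| Mortality ICC+MISA / DCC+MISA | Mean difference (days) | Median difference (days) | p < 0.05, all infants | p < 0.05, survivors only |
|---|---|---|---|---|
| 5% / 3.5% | 0.84 | 0.45 | 4.5% | 4.6% |
| 10% / 7% | 1.56 | 0.95 | 6.0% | 4.7% |
| 15% / 10.5% | 2.56 | 1.53 | 8.3% | 5.1% |
| 20% / 14% | 3.20 | 2.07 | 10.9% | 5.2% |
| 30% / 21% | 4.95 | 4.17 | 21.1% | 4.4% |
| 15% / 15% | −0.05 | 0.01 | 5.0% | 5.1% |

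There is no true difference in stay in any row. With equal mortality the distortion disappears, so differential death is its source. The survivors-only column stays near 5% because the simulation makes deaths unrelated to stay. In practice, infants saved by better care may be the sickest, and survivors would then not be comparable.

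**The case against.** Three stronger readings are tempting, and the document supports none of them.

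- **That the plan states deaths are kept in the duration comparisons.** It does not say so. This follows only from listing raw durations, naming tests by data type and setting no restriction. A fuller protocol or analysis plan could contain a rule. What remains is that the article fixes the form of the outcome and the test, and neither handles death. Dropping deaths without saying so would give a survivors-only comparison with its own selection problem.
- **That raw IMV duration penalises the better-surviving group.** As shown in the working, the direction can go either way, and the article has no data to settle it.
- **That the plan predicts better survival with DCC+MISA.** The 30% figure is background on DCC in preterm infants generally. The Discussion calls the benefit in the most premature infants unclear, and the sample size assumes a change in BPD only. Survival may differ, but no difference is assumed.

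Two further objections carry weight. Several exclusions (haemorrhagic shock, early-onset sepsis, air leakage, stopped treatment) probably remove some infants at high risk of early death, which would shrink the effect. And mortality is reported beside the durations, so a careful reader has some warning. That warning does not repair the test, because its p-value still mixes the two effects.

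**Conclusion.** The point holds in a limited form. As written, the duration outcomes let early deaths count as short times for stay, oxygen and non-invasive support, and this can work against a group with better survival. For IMV, only the mixing of death with exposure is established, not the direction.

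The size rests on assumed mortality and durations. Over 5% to 30% control mortality with a 30% relative reduction, the spurious difference in mean stay is 0.8 to 5.0 days. The rejection rate runs from about nominal (4.5% and 6.0% at 5% and 10% mortality) to 21.1% at 30%. If mortality is low or similar between groups, the effect is small or absent. The outcomes are secondary, so the BPD comparison and the sample size are untouched. The change should be made but is not critical.

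**What to change.** For the respiratory durations, adopt one of two definitions and state it before the prospective cohort is analysed:

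- keep the rank test and give in-hospital death the worst rank; or
- use days alive and free of IMV, of respiratory support and of oxygen over a window of the same length for every infant, for example the first 28 days, with death scored zero.

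The window should not end at 36 weeks corrected age, because its length would then depend on gestation: 13 weeks (91 days) for an infant born at 23+0 weeks, but 6 weeks and 1 day (43 days) at 29+6. A 23-week survivor with 45 days of support would score 91 − 45 = 46, ahead of a 29+6-week infant who never needed any (43). An unadjusted rank test would carry that into the comparison.

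Report raw durations, length of stay and cost in survivors to discharge as description, beside each group's mortality.

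The cost is a redefinition of a few secondary outcomes from support and survival data already planned, with no extra infants. A measure that includes death is slightly harder to read, and a fixed early window leaves out later support, which the survivor-only durations still show. Neither option removes confounding between the three periods.

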**Figure 1 F1:**
[figure not shown]
Flow chart nof the study. This study is a single-center ambispective cohort study involving hospitalized preterm infants in the NICU of Peking University Third Hospital from Jan. 1, 2017, to Oct. 31, 2027. The subjects from Jan. 1, 2017, to Dec. 31, 2024, were included in the retrospective cohort study, while a prospective cohort study was conducted from Aug. 31, 2025 to Oct. 31, 2027.

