### Research grouping

Patients were divided into three groups based on the study's time phases and the differences in treatment they received after birth:

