#### ICC+tracheal intubation group

From Jan.1, 2017 to Dec. 31, 2020. Umbilical cord clamping occurs within 20 s after birth. Infants are diagnosed with NRDS and receive a therapeutic dose of PS via tracheal intubation within the first 12 h after birth.

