#### ICC+MISA group

From Jan.1, 2021 to Dec. 31, 2024.Umbilical cord clamping is performed within 20 s after birth. Infants are diagnosed with NRDS and receive a therapeutic dose of PS via MISA within the first 2 h after birth.

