#### DCC+MISA group

From Aug. 31, 2025 to Oct. 31, 2027. Infants without contraindications to DCC, as determined by prenatal evaluation, receive immediate non-invasive respiratory support after birth. DCC is successfully performed for 60 s, followed by a diagnosis of NRDS. A therapeutic dose of PS is administered via MISA within the first 2 h after birth.

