### Data collection and diagnoses

Demographic data will include gestational age, birth weight, sex, multiple births, antenatal corticosteroid use, mode of delivery, maternal complications, Apgar score, and cord blood gas levels. Clinical data will encompass survival rates, required doses and timing of surfactant administration, blood gas measurements on the first day after birth, need for mechanical ventilation during hospitalization, duration of NCPAP/NIPPV, days on supplemental oxygen, hospitalization costs, and morbidity of BPD, pneumothorax, nasal trauma, pulmonary hemorrhage, hsPDA, IVH, PVL, blood culture-confirmed late onset sepsis, NEC, and ROP.

Pneumothorax will be diagnosed by the presence of air in the pleural cavity in a chest x-ray. Pulmonary hemorrhage will be diagnosed based on the gushing of bloody fluid from the upper airway or endotracheal intubation and when the chest x-ray is consistent with the relevant clinical findings. The diagnosis for hsPDA will be based on clinical signs and echocardiogram. IVH and white matter injury will be diagnosed by cranial ultrasound examination, and IVH will be graded by the Papile classification system. Blood culture-confirmed sepsis will be defined as clinical sepsis with evidence of pathogens in blood culture. NEC will be graded according to the modified Bell's classification system. The diagnosis and staging of ROP will be based on retinal examination by a consultant ophthalmologist.

Pneumothorax will be diagnosed radiographically by detecting air within the pleural cavity on chest radiography. Pulmonary hemorrhage is defined as acute onset of frank blood emanating from the upper airway or endotracheal tube, accompanied by radiographic evidence concordant with clinical manifestations. The diagnosis of hsPDA will be established through integration of clinical indicators and confirmatory echocardiography (13). IVH and PVL will be identified via standardized cranial ultrasonography, with IVH severity classified according to the Papile grading system (14). Culture-confirmed late-onset sepsis requires both compatible clinical signs and isolation of pathogenic microorganisms from blood cultures. NEC will be staged using the modified Bell's classification criteria (15). ROP diagnosis and staging will be determined through comprehensive retinal evaluations performed by a certified ophthalmologist.

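### Hospitalization cost is compared across three non-overlapping calendar periods with no stated price year or deflator, so any change in price level would be read as an effect of the treatment strategy

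*Protocol article*

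**What the plan says.** Under Secondary outcome measures, one item combines length of stay with cost: length of "hospitalization and associated costs for care" and treatment. Data collection and diagnoses lists "days on supplemental oxygen, hospitalization costs, and morbidity of BPD" among the clinical data. Neither place gives a currency, a price year or a unit of resource use.

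Research grouping ties group to calendar time: "Patients were divided into three groups based on the study's time phases and the differences in treatment they received after birth". The windows are:
- ICC+tracheal intubation: "From Jan.1, 2017 to Dec. 31, 2020"
- ICC+MISA: "From Jan.1, 2021 to Dec. 31, 2024"
- DCC+MISA: "From Aug. 31, 2025 to Oct. 31, 2027"

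The Figure 1 legend gives the overall span as "from Jan. 1, 2017, to Oct. 31, 2027".

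Statistical analysis sends normally distributed data to one-way ANOVA with Student-Newman-Keuls post hoc tests. For other continuous data, "intergroup comparisons are made using the Kruskal–Wallis test". Confounder adjustment is described only as logistic regression for binary outcomes, and the adjusted odds ratio is for BPD. The Discussion concedes possible bias from differing years of hospitalization. It offers two safeguards: a limit on how far back the retrospective cohort goes, and common eligibility criteria.

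**The concern.** A cost is a quantity of care multiplied by a price. If prices differ between periods, identical care produces different costs. The periods do not overlap here, so every infant in a group carries that group's price era. The stated tests have no way to separate the two sources of difference.

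Covariate adjustment at the analysis stage cannot repair this, because a term for calendar period would coincide with the group variable. The repair has to sit in the definition of the outcome. Neither safeguard in the Discussion bears on prices: common eligibility criteria do not change a tariff, and limiting the look-back does not put the remaining years on one price level.

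At stake is the reading of one secondary outcome. The Abstract says the comparison of the three strategies is meant to inform treatment decisions. A cost saving or excess that is only price drift, or a real saving hidden by it, would mislead that use.

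**Working it through.** **Group sizes.** The article gives no figure for cost, so the numbers per group come from its BPD sample size. With p1 = 0.29, p2 = 0.14, k = 3, z = 1.96 and 0.84:

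n2 = (1.96 + 0.84)² × [0.29 × 0.71/3 + 0.14 × 0.86] / 0.15² = 7.84 × 0.18903 / 0.0225 = 65.87, rounded up to 66, and n1 = 3 × 66 = 198.

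Allowing for 10% loss, 66/0.9 = 73.3, rounded up to 74, and 3 × 74 = 222. The stated figures reproduce.

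**Price gap.** This uses the dated windows in Research grouping and assumes even accrual within each.
- Midpoints: about 1 January 2019, 1 January 2023 and 30 September 2026.
- Intubation to ICC+MISA: 4.00 years.
- ICC+MISA to DCC+MISA: 3.75 years. This is the pair the study is sized on.
- Intubation to DCC+MISA: 7.75 years.

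The Abstract and Study design describe the ICC+MISA period as 2021 to 2025. If it ran to the day before the prospective window opens (242 more days), its midpoint would move by 121 days. The 3.75-year gap would then shorten by about a third of a year, which does not change the picture.

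**Spurious difference with identical care.** For an assumed annual price change r, the false relative difference is (1 + r)^gap − 1. The documents give no value for r, so a range is shown.

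| Assumed r per year | DCC+MISA vs ICC+MISA | DCC+MISA vs intubation |
|---|---|---|
| −2% | −7.3% | −14.5% |
| 0% | 0% | 0% |
| 1% | 3.8% | 8.0% |
| 3% | 11.7% | 25.7% |
| 5% | 20.1% | 45.9% |

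**Chance of a false finding.** This is a two-sided normal approximation on log cost at the 5% level, with no true difference in care. The SD of log cost is not in the documents and is assumed to be 0.5.

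- Standard error for 198 vs 66: 0.5 × √(1/198 + 1/66) = 0.0711.
- At r = 3%: shift = 3.747 × ln 1.03 = 0.1107, ratio to standard error 1.56, chance of p < 0.05 about 34%.
- At r = 1%: shift = 3.747 × ln 1.01 = 0.0373, ratio 0.52, chance about 8%.
- At r = 2% and 5%: about 18% and 73%.
- Sensitivity to the SD, from 0.4 to 0.8: 50% down to 16% at r = 3%, and 10% down to 6% at r = 1%.
- DCC+MISA vs intubation, also taking 198 for the intubation group and SD 0.5: about 19% at r = 1% and 90% at r = 3%.

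These are pairwise figures. They indicate the size of the problem and are not the exact error rate of the three-group test.

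**The case against.** The strongest objection is that the article never says costs are compared in nominal currency. Price year and deflator for one secondary outcome are details that a condensed article may leave to a fuller protocol or analysis plan, which is not shown. This stands in part. A reader might infer that raw billed amounts go straight into the tests, but that rests only on the article's silence. The point is therefore limited to what the article does fix: the outcome, the grouping by period and the unadjusted tests. Followed as written, these cannot separate price from strategy.

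Two further strong readings are not supported. A reader might take the span in the Figure 1 legend, about 10.8 years from first to last day, as the amount of price change in the comparison. No pair of groups is that far apart on average; the midpoint gaps are 3.7 to 7.7 years. A reader might also conclude that the cost result must be wrong whatever the treatments do. That needs a non-zero price trend, and the documents give none. At 1% a year the false-positive chance for the sized pair is about 8%, not far above the nominal 5%.

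It is also fair to say that length of stay, IMV duration, NCPAP/NIPPV duration and oxygen days are compared in physical units, which prices do not affect. A careful reader could use them to check a cost difference. The Discussion also admits era bias in general terms. Both points lower the stakes, but neither corrects the cost comparison itself.

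**Conclusion.** The point holds in a limited form. Cost is compared without adjustment between groups that are fully confounded with calendar period, no common price level is stated, and the safeguards listed against era bias do not reach prices.

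The size depends on a price trend that the documents do not give. At 1% to 5% a year the spurious difference would be about 4% to 20% for DCC+MISA against ICC+MISA and 8% to 46% against intubation. It would be nil with flat prices and opposite in sign with falling ones. With a log-cost SD of 0.5, 198 vs 66 infants and no true difference, the sized pair would reach p < 0.05 in about 8% of studies at 1% a year and 34% at 3% a year. An actual distortion cannot be shown from the documents, nor can its direction.

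The primary outcome and the sample size are untouched. This is an inexpensive improvement to one secondary outcome, and it is best settled before the 2025 to 2027 costs are seen.

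**What to change.** Define the cost outcome in one of two ways:
- Restate every hospitalization cost in constant prices of one named reference year, using a named published price index.
- Value each infant's recorded resource use (length of stay, ventilation days, surfactant doses, transfusions) at one fixed price list applied to all three groups.

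Compare those amounts between groups and report nominal cost descriptively only. If a fuller protocol or analysis plan already fixes a price basis, stating it in one sentence is enough.

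The index route takes one sentence in the plan and a multiplication applied to stored data. The price-list route uses mostly data already planned: length of stay, IMV and NCPAP/NIPPV duration and surfactant doses are all listed. For transfusions the article lists timing, so counts may have to be extracted as well. The downside of either route is that an index or price list only approximates this hospital's own prices. Naming it in advance keeps that choice independent of the results.

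### The only transfusion outcome is the timing of transfusions, which exists only for transfused infants and does not measure the need for transfusion

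*Protocol article*

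**What the plan says.** **Outcome.** The list under Secondary outcome measures contains one item on transfusion. It pairs haemoglobin and haematocrit within 24 h with "and timing of blood transfusions during" hospitalization. No section names the proportion transfused, the number of transfusions or the volume as an outcome.

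**Expected effect.** The Background says of DCC that it "minimizes the need for blood transfusions", alongside effects on blood volume, iron stores and neurodevelopment.

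**Data.** The clinical data listed under Data collection and diagnoses include "required doses and timing of surfactant administration, blood gas measurements on the first day after birth, need for mechanical ventilation during hospitalization". Transfusion is not in that list.

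**Analysis.** Normally distributed data go to one-way ANOVA. For the rest, "Non-normally distributed data are expressed as median (Q1, Q3), and intergroup comparisons are made using the Kruskal–Wallis test". Categorical data are compared by "employing the *χ*² test with continuity correction or Fisher's exact test as appropriate". The section gives no time-to-event method and no rule for infants without the event.

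**The concern.** Need for transfusion is a matter of whether and how often an infant is transfused. Timing answers a different question, and only for infants who were transfused. Those infants form a subset selected after birth, by an event that the Background says cord management changes. The transfused DCC infants and the transfused ICC infants are therefore not comparable subsets, even if the full groups were.

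Which way this pushes the result depends on which transfusions DCC prevents. If it mainly spares infants who would have been transfused late, those still transfused in the DCC group are the early ones, and DCC appears to bring transfusion forward. If it mainly prevents early transfusions, or delays all of them, the difference goes the other way. At stake is the interpretation of one secondary outcome, but it is one on which DCC has a direct and plausible effect.

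**Working it through.** **1. Group sizes.** The plan computes no figure for transfusion. The check borrows its group sizes, so those are reproduced first. Inputs from Sample size calculation: "Assuming the BPD incidence rate (p_1_) in the ICC + MISA group for this study is 29"%; the DCC + MISA rate "decreases by 15%–14"%, read as a fall of 15 points to 14%; z values 1.96 and 0.84; k = 3.

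n2 = (1.96 + 0.84)² × [0.29 × 0.71 / 3 + 0.14 × 0.86] / 0.15² = 7.84 × 0.18903 / 0.0225 = 65.87, so 66, and n1 = 3 × 66 = 198. With 10% loss, 66 / 0.9 = 73.3, so 74, and 3 × 74 = 222. The stated figures reproduce, and the point does not depend on them.

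**2. Assumed models.** All transfusion rates and days below are assumptions; the documents give none. Each run compares 222 ICC + MISA with 74 DCC + MISA infants, two-sided at 5%. Timing is compared among transfused infants by the rank test (the two-group form of Kruskal-Wallis). The proportion transfused is compared over all infants. The third group and confounding by calendar period are left out.

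**3. Model A: log-normal day of first transfusion.** Median day 20, log-SD 1, 60-day stay.

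- ICC, ever transfused: Φ(ln(60/20)) = Φ(1.099) = 0.864. Median day among the transfused: Φ(z) = 0.432, z = −0.171, 20 × e^(−0.171) = 16.9.
- DCC prevents half of the transfusions due after day 20. Ever transfused: 0.5 + 0.5 × 0.364 = 0.682. Median: Φ(z) = 0.341, z = −0.410, 20 × e^(−0.410) = 13.3.
- DCC prevents 20% regardless of day. Ever transfused: 0.8 × 0.864 = 0.691. Median unchanged at 16.9.
- DCC delays all transfusions by a factor of 1.5. Ever transfused: Φ(ln(40/20)) = Φ(0.693) = 0.756. Median: Φ(z) = 0.378, z = −0.311, 1.5 × 20 × e^(−0.311) = 22.0.

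| Assumed DCC effect | Timing significantly earlier under DCC |
|---|---|
| Half of late transfusions prevented | about 40% of studies (38% to 40% across runs) |
| A quarter of late transfusions prevented | about 11% |
| Half of late prevented, plus 1.25-fold delay | about 6% |
| 20% prevented regardless of day | about 3%, near the chance rate |
| Half of late prevented, plus 1.5-fold delay | under 1% |
| 1.5-fold delay only | about 0% (significantly later in about 50%) |

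Fewer DCC infants are transfused in every row. In the first row, Fisher's test on the proportion transfused finds the benefit in about 90% of studies.

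**4. Model B: an early and a late component.** Under ICC 60% are transfused: 25% early (median day 5, log-SD 0.5) and 35% late (median day 28, log-SD 0.3). The median day among transfused ICC infants is about 20. The last column uses the chi-square test with continuity correction.

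| Assumed DCC effect | Transfused under DCC | Median day, DCC | Sig. earlier | Sig. later | Benefit found on proportion |
|---|---|---|---|---|---|
| None | 60% | 19.5 | 2% | 3% | 2% |
| Late 35% to 25% | 50% | 14.7 | 12% | under 1% | 27% |
| Late 35% to 20% | 45% | 11.4 | 23% | under 1% | 57% |
| Late 35% to 15% | 40% | 8.9 | 41% | 0% | 81% |
| Late 35% to 10% | 35% | 7.0 | 67% | 0% | 95% |
| Late 35% to 20%, plus 3-day delay | 45% | 14.6 | 0.5% | 5% | 57% |
| Early 25% to 10% | 45% | 25.1 | 0% | 40% | not run |

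**5. Reading.** In both models fewer DCC infants are transfused, yet the timing difference can have either sign or vanish. Wherever the proportion was also tested under a DCC effect in model B, it pointed to the benefit more often than timing differed significantly in either direction.

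**The case against.** **The word may be a slip.** *Timing* could stand for *times*, meaning the number of transfusions, and the article has other language slips. On that reading the outcome is a count and the conditioning argument falls away. This cannot be excluded. But the data list uses *timing* of surfactant administration where it plainly means when, and nothing in the article settles the matter. On either reading the wording needs attention.

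**The analysis is partly inferred.** The article does not say that untransfused infants will be dropped. Time to first transfusion over all infants would be a legitimate form of the outcome, and a fuller plan might specify it. That is fair. Still, the article fixes the variable, and the methods it names for a continuous variable use observed values. A time-to-first-event analysis would also leave the number of transfusions unmeasured.

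**The Background is not a promise.** Iron stores and neurodevelopment are cited there too and are not outcomes, while the hypothesis and sample size concern BPD. So there is no contradiction in the strict sense. The mismatch is that transfusion was chosen as an outcome, in a form that misses the stated effect.

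**Two stronger readings are tempting.** A reader might infer that the plan will make a real benefit look like harm. The documents do not support this. They give no transfusion rates, and the apparent harm largely disappears once prevention is unrelated to day or some delay is added. A reader might also infer that the study cannot report the need for transfusion. That goes too far as well: records that give the timing also show who was transfused and how often, and early haemoglobin and haematocrit are measured without conditioning on transfusion.

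**Conclusion.** The point holds for the outcome as worded. Analysed by the article's methods for continuous data, it compares subsets selected by a post-birth event that cord management is expected to change, and it does not measure the need for transfusion. The sign of a timing difference does not identify benefit.

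The numerical size rests entirely on assumed transfusion rates and days. Significantly earlier timing under DCC appeared in about 0% to 40% of simulated studies across most scenarios, and in 67% in the one with the largest assumed fall (60% to 35% transfused, all of it in late transfusions). These figures illustrate the mechanism and do not forecast this study's result. The consequence is confined to one secondary outcome; the primary outcome and the sample size are unaffected. The change is worth making because it is specific and nearly free.

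**What to change.** Under Secondary outcome measures, replace the transfusion item with two outcomes, each compared over all infants in the group:

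- the proportion of infants with at least one transfusion during hospitalization;
- the number of transfusions per infant, counting zero for the untransfused.

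Add transfusion (given or not, number, dates) to the list under Data collection and diagnoses. Keep age at first transfusion as descriptive only. If *timing* was meant as *times*, correct the word and state that untransfused infants count as zero.

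The cost is a change of wording. Any record that gives the timing of transfusions also gives these counts, for the retrospective groups as well. The DCC + MISA period runs to October 2027, so the change can be made before the comparison is run.
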